### Measures

#### Diagnostic Evaluation

The MINI 7.0 for Diagnostic and Statistical Manual of Mental Disorders-5 is one of the most widely used diagnostic instruments to reliably determine psychiatric disorders in clinical populations [42-45]. The MINI is designed to be used by clinicians but can be administered by nonclinicians with appropriate training and supervision. The recruiters conducting the screening, the nurse interventionists, and the IA received training and weekly supervision on the MINI.

#### Primary Outcomes

##### Depression

The nurse interventionists at baseline and the IA at the follow-up assessments complete the HAM-D [46], one of the most widely used clinical measures of depression in psychiatric research that has strong psychometric reliability and validity. It has also been used in several antidepressant medication trials in South Africa [45,47,48]. Assessors are trained by certified trainers and licensed psychiatrists/psychologists on the study. The self-reported Center for Epidemiologic Studies Depression Scale [49] is also used. This measure has been translated into isiXhosa and used successfully in South Africa.

##### Assessment of Adherence to Antiretroviral Therapy

Wisepill is a real-time, electronic adherence monitoring system that comprises a pillbox container fitted with a global system for mobile communication chip. Using mobile phone technology, the Wisepill transmits a real-time signal to the Wisepill Web server each time the pillbox is opened. The Wisepill Web server can be securely accessed from any computer via the Wisepill Technologies website with the use of a designated log-in and password. It captures real-time data on device openings and, hence, provides the results of weekly assessments for longitudinal modeling. For the purposes of this study, we did not establish a *window* for missed doses; they were just counted as whether or not they opened the device the required number of times (ie, if they opened the device on 2 separate occasions for a twice daily regimen, it would be counted as fully adherent for the day, and if they opened it once for a twice daily regimen, it would be counted as 50% for the day). To ensure the Wisepill device is working properly, we check in with participants at approximately half-way between major study visits (ie, at approximately 2, 6, and 10 months in study participation). In addition, we monitor Wisepill functionality between the baseline visit (when the device is issued) and the randomization visit. To ensure the device is working properly, if no signal is detected from the Wisepill device for 3 or more days in a row within the first week after the device has been issued, we contact the participant to ascertain if they are experiencing any issues with their device. The purpose of these check-ins is solely to enquire about any difficulties using the Wisepill device. The Wisepill Web server also monitors device battery levels, and participants whose devices had low battery are contacted to remind them to charge the Wisepill device.

#### Secondary Outcomes: HIV Viral Load and CD4 Cell Count

Absolute CD4 cell count and number of HIV viral copies per milli liter of blood are extracted from the participants’ medical record at baseline (to assess the first-line treatment failure inclusion criteria) and at 12-month follow-up. This allows for a calculation of the proportion of patients with virologic suppression. Participants who do not have viral load test results within 1 month of the baseline assessment or 4-, 8-, and 12-month follow-up undergo a blood draw for assay using the COBAS AmpliPrep/TaqMan HIV-1 test (range: 20-10,000,000 copies/mL) [50].

#### Psychosocial Self-Report Assessment Battery

Participants complete a demographic questionnaire including items regarding age, sex, sexual orientation, educational history, and employment status. National Institutes of Health (NIH)–defined categories are used to assess participant race and ethnicity, although we anticipate mostly (if not only) isiXhosa-speaking black South African participants. We also obtain data on mode of HIV infection, using a single-item (AIDS Clinical Trials Group) question assessing risk factors for likelihood of means of HIV infection.

#### Medications

During baseline assessment, participants will provide information regarding all of their medications (psychiatric, HIV, and other). When completing assessments at every study visit thereafter, patients are asked to report any changes to their medication regimen. These changes are recorded on adherence questionnaires and cross-checked with clinic chart review. Any initiation or changes to antidepressant medications are tracked across all participants and will be used as covariates in analyses.

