## Methods

### Trial Design

Project Ziphamandla (meaning *to be empowered* in isiXhosa) is a 2-arm, randomized controlled trial comparing CBT-AD with ETAU among PLWH who are failing, or have failed, first-line ART (see Consolidated Standards of Reporting Trials diagram in Figure 1).

Before randomization to treatment condition, participants complete a diagnostic assessment, clinician-rated measures of depression, and a self-report psychosocial assessment battery. We aim to randomize 160 participants to either CBT-AD (8 sessions) or ETAU. For participants in both conditions, treatment providers receive letters summarizing the results of the participants’ diagnostic assessments. At this point, their treatment providers may further diagnose or treat (with antidepressants) MDD in the participants. Randomization follows approximately 1 month after the baseline assessment, so that stratification can occur by those who may or may not have commenced antidepressants as part of their care, following this letter. The 1-month period from baseline to randomization also allows for a baseline assessment of ART adherence using Wisepill real-time electronic adherence monitoring. For participants in both arms, there are 4 major study assessment points: baseline, post intervention (4-month), 8-month, and 12-month.

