#### Randomization

Approximately 1 month after the initial baseline assessment, participants return for their randomization visit. At this visit, participants are randomly assigned to either CBT-AD or ETAU. Randomization is determined by a computer-generated chart, using the Research Electronic Data Capture (REDCap) randomization module [31]. Study staff enter stratification information (specifically, antidepressant use and site) and click randomize. Antidepressant use is confirmed by paper medical record review. Once the condition has been assigned in REDCap, this field is locked and cannot be changed.

As the study team sends a letter to HIV providers documenting the participants’ depression, regardless of study arm, participants are given the opportunity to start using antidepressant medication outside of the study if they are not already using them. Therefore, at the randomization visit, we stratify randomization by whether or not the participant is taking an antidepressant (2 levels). We are also stratifying by which study site the participant is seen at (2 levels). Note our Data Safety and Monitoring Board (DSMB) reviews baseline data annually for adequacy of randomization.

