#### Standard of Care—Enhanced Treatment as Usual

The clinic nurse provides feedback to the participant and to their clinic doctor (via a letter) about their MDD diagnosis. In addition, all participants undergo standard of care adherence counseling in the clinic, which may include several sessions with a clinic counselor. The letter specifically states that they are not restricted in terms of referral or treatment of MDD for their patient with respect to antidepressant medications or other interventions available.

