#### Secondary Outcome Measures

Secondary outcome measures include viral load, analyzed categorically (suppressed vs not) at the 12-month outcome, using <400 copies/mL as suppressed (consistent with recent work analyzing chart-extracted viral load data from the same clinics in Khayelitsha). CD4 is analyzed continuously at the 12-month outcome. In addition, HIV medication adherence and depression scores over time are examined as secondary outcomes using the 4-, 8-, and 12-month assessment time points.

The ultimate data analytic approach will depend on the distribution of the data. We anticipate that we will use generalized linear models), which are estimated using generalized estimating equations with robust standard error estimates to account for repeated measures of the outcome. For the primary outcomes, we will examine adherence scores longitudinally using the Wisepill data and Hamilton scores using the 2 time points (baseline to 4 months) comparing the 2 study arms. For outcomes assessed at the 4 major assessments (ie, baseline and 4, 8, and 12 months), we will use repeated measures analyses. For 12-month viral load, we will test the proportion of those who are suppressed using Fisher exact test. If continuous viral load data are analyzed, we will make log transformations and examine viral load using repeated measures. To reduce bias, the intention-to-treat principle is utilized, where individuals are analyzed according to the condition they were randomized, regardless of their fidelity to that condition.

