Potential challenges to the success of this trial include difficulties in identifying and recruiting individuals in busy clinic settings, with both virological failure and MDD. To successfully randomize participants, we confirm that the 1-month viral load is >400 copies and that criteria for MDD are met. To address this challenge, we make allowance for additional blood draws in depressed individuals. We work tirelessly with clinic staff in their busy HIV clinics to identify potential participants. A second potential challenge is participant retention through both the acute (intervention) component and the long-term (12 months) outcome period. In this study, PLWH live in periurban areas and may struggle to attend regular planned therapy visits because of casual employment, sickness, or migration. We ensure that we obtain maximal and contemporaneous contact information and work hard to develop rapport with participants across the study. Participants who miss visits are tracked through the clinic system and approached on visit days, and those who migrate may be allowed to complete major assessments by telephone. Hopefully, this will mitigate the risks of attrition. Finally, although previous studies have reported limited or variable success with task-shared behavioral interventions because of poor fidelity, limited skills, or insufficient supervision, major components of this study are intervention supervision (which is performed weekly in a face-to-face fashion), fidelity assessment, and session monitoring. We also note that although we are stratifying for antidepressant prescription across both arms, it is possible that the study itself may result in a change in prescribing behavior. We do not anticipate that this will be a marked effect but will report on this when a final medical record review is conducted at study completion.

In summary, this study has the potential to address several key questions regarding how effective behavioral interventions might be delivered and integrated into primary health care settings in LMIC with high HIV prevalence. Our findings might be used to inform how patients with adherence difficulties and HIV nonsuppression might be effectively treated in primary care, which is critical to motivating to health authorities for scale-up.

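### Antidepressant starts and changes after randomization are to be used as covariates, so a comparison adjusted for them would not estimate the total effect of assignment to CBT-AD

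*Protocol article*

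**What the plan says.** All references are to the protocol article.

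- **Medications (Measures).** Medications are listed at baseline. After that, "When completing assessments at every study visit thereafter, patients are asked to report any changes to their medication regimen". The rule at issue follows: "Any initiation or changes to antidepressant medications are tracked across all participants and will be used as covariates in analyses".
- **Trial Design.** "Randomization follows approximately 1 month after the baseline assessment". Only changes in that first month come before assignment; those reported at 4, 8 and 12 months come largely or wholly after it.
- **Randomization.** Antidepressant use at the randomization visit is already a design variable: "we stratify randomization by whether or not the participant is taking an antidepressant (2 levels"). Site is the other stratification factor.
- **Standard of Care—Enhanced Treatment as Usual.** The letter to providers says that "they are not restricted in terms of referral or treatment of MDD for their patient with respect to antidepressant medications". Trial Design and Randomization make clear that the letter is sent for participants in both arms.
- **Secondary Outcome Measures (Data Analysis).** "the intention-to-treat principle is utilized, where individuals are analyzed according to the condition they were randomized". The same section anticipates generalized linear models fitted by generalized estimating equations, and a Fisher exact test for 12-month viral suppression.
- **Discussion.** The authors accept that "it is possible that the study itself may result in a change in prescribing behavior", do not expect this to be marked, and promise to report it after a final record review.

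**The concern.** An antidepressant started or changed after randomization may be a response to what happened under the assigned treatment. Someone who improves gives the provider less reason to prescribe; someone who stays depressed gives more. Such a variable can lie downstream of arm and also share causes with the outcome.

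Putting it in the model does two things. It removes any part of the arm difference that runs through prescribing. It also compares participants within levels of a variable that unmeasured severity helped to determine, and the arms need not be alike within those levels. Randomization protects the comparison of arms as assigned. It does not protect the comparison within strata formed later.

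At stake are the HAM-D comparison, which is a primary outcome, and any adherence comparison modelled with the same covariate. The trial sets out to learn what assignment to CBT-AD does when providers in both arms prescribe as they see fit. The adjusted coefficient answers a different question.

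**Working it through.** The protocol states no figure on this point, so there is none to reproduce. The check has a textual part and a numerical illustration.

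**Text.** Four features matter together: the covariate covers any start or change; recording continues at all visits after baseline; assignment happens about one month in; and no analysis is exempted. Read as written, the rule includes post-randomization changes.

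**Illustration A: start rates fixed by arm.** Inputs from Sample Size Considerations: a medium effect (read as 0.5 SD, an assumption) and a within-subject correlation of 0.5, used as the baseline–outcome correlation. Inputs not in the documents, all assumed: start rates by arm; a drug effect on HAM-D of 0 or -0.4 SD; a correlation of 0 or 0.5 between the propensity to start and a latent prognosis, which itself correlates 0.5 with outcome.

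In an additive linear model with baseline independent of arm and of starting,

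adjusted effect = total effect − γ × (p_CBT − p_ETAU),

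where p is the proportion starting and γ is the coefficient of starting in the adjusted model.

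- *Drug effect only:* γ = -0.4. For 30% ETAU and 10% CBT-AD, bias = −(−0.4)(0.10 − 0.30) = -0.08. For 40% and 10%, −(−0.4)(−0.30) = -0.12.
- *Prognosis only:* γ = 0.5 × 0.5 × (φ_ETAU + φ_CBT) / (p_ETAU q_ETAU + p_CBT q_CBT), where q = 1 − p and φ is the normal density at the threshold for starting. For 30/10: 0.25 × (0.3477 + 0.1755)/(0.21 + 0.09) = 0.436, so bias = −0.436 × (−0.20) = +0.087. For 40/10: 0.25 × (0.3863 + 0.1755)/(0.24 + 0.09) = 0.426, so bias = +0.128.
- *Both, 30/10:* γ = 0.436 − 0.4 = 0.036, so bias = +0.007.

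A simulation of 400,000 subjects per scenario agrees:

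| Start rates ETAU/CBT-AD | Drug effect only | Prognosis only | Both |
|---|---|---|---|
| 20/20% | -0.002 | 0.001 | -0.002 |
| 30/10% | -0.081 | +0.085 | +0.008 |
| 40/10% | -0.122 | +0.127 | +0.010 |
| 10/30% | +0.078 | -0.087 | -0.004 |

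Entries are bias in SD when the true effect is -0.50; a negative sign exaggerates the benefit. With a true effect of zero, 40/10% gives -0.119 or +0.123, a spurious difference. Adjusting for baseline alone recovers the truth to within about 0.01 in every scenario.

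**Illustration B: starting driven by persisting severity.** Severity S = −0.5T + U, with T = 1 for CBT-AD and U normal with SD 0.7. The log-odds of starting rise by 1, 1.5 or 2 per unit of S, with 30% starting in ETAU. HAM-D = S − (drug effect) × start + residual, with residual SD 0.71. All of these inputs are assumed.

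- *Without baseline HAM-D:* with no drug effect the adjusted estimates run from about -0.46 to -0.40 (8–20% attenuation). With a 0.3 SD drug effect, attenuation is about 3–13% against totals of -0.47 to -0.46.
- *With a baseline correlated about 0.5 with outcome:* with no drug effect, about -0.48 to -0.45 (4–11%, from unrounded values). With a 0.3 SD drug effect, about -1% to 4% against totals near -0.47.

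The second set is closer to the planned analysis, which uses baseline and 4 months. It lets baseline track the persisting-severity component; if baseline tracks that less closely, more attenuation remains. It is an illustration, not a bound. Nothing was computed for adherence, where the same reasoning applies.

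**The case against.** Several points on the other side stand.

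- The sentence is in a measurement section and speaks of analyses in general. The Data Analysis section gives no covariate list for the primary models and leaves the final approach open. A reader might infer that the primary estimate is certain to be biased. The document does not settle that: it exempts no analysis, but it does not name the primary model either.
- The same sentence covers starts in the month before randomization. Adjusting for those is sound, and the delay and stratification were designed to capture them.
- The Fisher exact test takes no covariates, so the rule cannot reach every analysis.
- A reader might infer that the intention-to-treat statement is breached. As the protocol defines it, participants are analysed in their assigned arm, and a covariate moves nobody. The objection is to the quantity estimated.
- A reader might infer that the provider letter belongs to ETAU alone, so that adjustment strips out the comparator. The letter goes out for both arms.
- A reader might infer that fewer CBT-AD participants will start a drug and that the effect will therefore be diluted. This is plausible, but the protocol gives no start rates, and the illustrations show bias of either sign.
- A fall in power from 80% at 0.50 SD to about 61% at 0.40 SD, with 64 per arm, can be computed. It takes the steepest assumed slope and a two-sample test without baseline. At 0.46 SD the same test has 73%.

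Two replies do not rescue the sentence. The authors' expectation of no marked change in prescribing comes with no figures, and their promise to report prescribing does not remove the covariate rule. An unseen analysis plan may well supply detail, but this is a stated rule, and a plan that follows it inherits the problem.

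**Conclusion.** The point holds in limited form. The protocol makes antidepressant starts and changes covariates without separating those before randomization from those after. Adjusting for the later ones means that a model-based HAM-D or adherence comparison no longer estimates the total effect of assignment.

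Size and direction cannot be derived from the document. Under the assumed inputs, bias is near zero when start rates are equal and selection into starting is the same in both arms, or when the two mechanisms offset. Otherwise it reaches about 0.1 SD either way (0.13 at most in the scenarios run) against a planned effect read as 0.5 SD. Because the sign is unknown, the adjustment cannot be defended as conservative. The conclusion that the estimated quantity changes rests on the text and needs none of these inputs; the magnitudes rest entirely on them.

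**What to change.** Replace the covariate clause in Medications with wording such as:

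> Antidepressant use at the randomization visit and site (the stratification factors), together with the baseline value of the outcome, are covariates in the model-based effectiveness analyses. Antidepressant initiation or change after randomization is reported by arm and is not a covariate in the primary or secondary effectiveness analyses; any analysis that accounts for it is labelled supportive or exploratory.

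Where a repeated-measures model keeps baseline as one of the responses, baseline should not also be entered as a covariate. The analysis plan should carry the same rule. Tracking of medication changes continues as now, and the by-arm report fits with what the Discussion already promises. The cost is one edited statement; no data, visits or sample size change.

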### Data Analysis

#### Primary Outcome Measures

The primary outcome analyses compare changes in depression (HAM-D; continuous measure assessed by a blinded assessor) and adherence scores (continuous measure assessed via Wisepill) from baseline to the 4-month assessment.

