### Trial Objectives

The goal of this trial is to investigate whether CBT-AD administered by nurses is effective for reducing depression and improving ART adherence among PLWH with adherence difficulties and MDD in primary health care in Cape Town, South Africa.

The primary objective is to compare the effectiveness of an isiXhosa-adapted, nurse-delivered CBT-AD intervention integrated into the HIV care setting in individuals who are failing, or have failed, first-line ART. The CBT-AD treatment is being compared with enhanced usual care (enhanced treatment as usual [ETAU]) at 12 months. ETAU consists of participants’ medical providers being furnished with a referral letter indicating the psychiatric conditions they meet diagnostic criteria for including MDD. Primary study end points include depression scores on the Hamilton Depression Scale (HAM-D; as assessed by a blinded assessor) at the 4-month assessment and changes in adherence scores (assessed via the electronic Wisepill device) between baseline and the 4-month assessment.

Secondary outcomes include HIV viral load and CD4 cell count at the 12-month assessment as well as adherence (Wisepill) and depression (HAM-D) over follow-up (4-, 8-, and 12-month assessments).

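### The HAM-D primary endpoint is a 4-month score in one place and a baseline-to-4-month change in another; a baseline-adjusted analysis of the 4-month score would reconcile them and gain about 7 to 10 points of power at the protocol's own correlation

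*Protocol article*

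**What the plan says.** **Endpoint.** Trial Objectives states: "Primary study end points include depression scores on the Hamilton Depression Scale (HAM-D; as assessed by a blinded assessor) at the 4-month assessment". The Abstract says the same. Both places describe change only for adherence.

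**Analysis.** Primary Outcome Measures applies change to both outcomes: "The primary outcome analyses compare changes in depression (HAM-D; continuous measure assessed by a blinded assessor", from baseline to the 4-month visit. The modelling paragraph, under Secondary Outcome Measures, plans to examine "Hamilton scores using the 2 time points (baseline to 4 months) comparing the 2 study arms". It expects generalized linear models "estimated using generalized estimating equations with robust standard error estimates to account for repeated measures of the outcome", and is openly provisional: "The ultimate data analytic approach will depend on the distribution of the data". Neither section names baseline HAM-D as a covariate.

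**Raters.** The Depression subsection states: "The nurse interventionists at baseline and the IA at the follow-up assessments complete the HAM-D".

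**Strata and covariates.** Randomization is stratified by antidepressant use at the randomization visit and by site: "We are also stratifying by which study site the participant is seen at (2 levels". The only covariates tied to the treatment comparison are in the Medications section: "Any initiation or changes to antidepressant medications are tracked across all participants and will be used as covariates in analyses". Site appears in no planned analysis.

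**Power.** Sample Size Considerations gives 160 randomized, a medium effect, correlation 0.5, 5% type I error and 20% attrition. The stated power for depression is just under 90% with full retention and 84% after attrition.

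**The concern.** The endpoint definition and the analysis statement do not match, and the version in the analysis section is the less efficient one. In a randomized trial, the 4-month score and the change from baseline have the same expected difference between arms, so the choice does not alter what is estimated on average. It alters precision. A two-time-point model with a separate baseline mean in each arm estimates the difference in change, and at a correlation of 0.5 subtracting baseline gains nothing over ignoring it. Using baseline as a covariate does gain.

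Two further details point the same way. The Primary Outcome Measures sentence attaches the blinded assessor to a change measure, yet nurse interventionists rate its baseline half. And randomization was restricted by two factors that the planned comparison does not clearly carry into the model.

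At stake are a wider confidence interval than necessary on a primary outcome and two possible readings of that outcome.

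**Working it through.** **Inputs from Sample Size Considerations:** N = 160; attrition 20%; correlation ρ = 0.5; type I error 5%.

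**Assumptions:** 1:1 allocation (80 per arm, 64 after attrition); two-sided test; medium effect taken as d = 0.5 on the SD σ of a single HAM-D score. The article gives neither a HAM-D SD nor a difference in points.

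**Formula.** With per-participant variance Vσ² and n per arm, power = Φ(0.5 / √(2V/n) − 1.96).

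- Change score: V = 2(1 − ρ) = 2(0.5) = 1.00
- 4-month score alone: V = 1.00
- 4-month score adjusted for baseline: V = 1 − ρ² = 1 − 0.25 = 0.75

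**Step 1: the plan's own figures, without baseline adjustment.**

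- Full retention, 80 per arm: 0.5 / √(2/80) = 3.162; Φ(1.202) = 88.5%. This fits just under 90%.
- After attrition, complete cases, 64 per arm: 0.5 / √(2/64) = 2.828; Φ(0.868) = 80.7%. This is 3.3 points below the stated 84%.
- After attrition, arm-by-time model that keeps all 80 baselines: variance per arm = (1 − ρ²)/64 + (1 − ρ)²/80 = 0.01172 + 0.00313 = 0.01484; 0.5 / √(2 × 0.01484) = 2.902; Φ(0.942) = 82.7%. This is within 2 points of 84%.

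The stated power is therefore close to what an unadjusted two-time-point comparison of change delivers.

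**Step 2: with baseline adjustment.**

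- 64 per arm: 0.5 / √(1.5/64) = 3.266; Φ(1.306) = 90.4%
- 80 per arm: 0.5 / √(1.5/80) = 3.651; Φ(1.692) = 95.5%

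The t-based calculation at 64 per arm gives 80.2% for change and 90.0% adjusted. A simulation of 20,000 trials gives 79.8% and 89.6%.

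**Step 3: the gain at ρ = 0.5.**

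- Against the complete-case change test: 90.4 − 80.7 = 9.7 points
- Against the repeated-measures change model: 90.4 − 82.7 = 7.7 points
- With full retention: 88.5% to 95.5%, 6.9 points before rounding
- Anchored on the stated 84%: Φ(2.954/√0.75 − 1.96) = 92.7%, a gain of 8.7 points

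The standard error falls by 1 − √0.75 = 13%. The same precision from a change score would need 1/0.75 = 1.33 times as many participants.

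**Step 4: sensitivity to the correlation (64 per arm, d = 0.5 on σ).**

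| ρ | Change, complete cases | Change, all baselines kept | Baseline-adjusted |
|---|---|---|---|
| 0.3 | 66.7% | 69.8% | 84.3% |
| 0.4 | 73.3% | 75.9% | 87.0% |
| 0.5 | 80.7% | 82.7% | 90.4% |
| 0.6 | 88.5% | 89.8% | 94.2% |
| 0.7 | 95.5% | 96.0% | 97.7% |

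If d = 0.5 is instead on the SD of the change score, the complete-case gain is 13.2 points at ρ = 0.3, 9.7 at 0.5 and 5.9 at 0.7.

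**Step 5: strata.** The antidepressant covariate in the Medications section is initiation or change, some of it after randomization. A participant already on an unchanged antidepressant belongs to the user stratum but has no initiation or change, so the covariate is not the stratum. The article does not say how much HAM-D variance the strata explain, so no power gain from them can be computed.

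**The case against.** The article condenses a fuller plan, and a covariate list is normally left to the SAP. The modelling paragraph is provisional, and a two-time-point model with a common baseline mean would be essentially equivalent to baseline adjustment. A change comparison is unbiased under randomization, and the plan claims 84% power. The endpoint recommended here is already the one in the Abstract and Trial Objectives.

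Much of this stands and limits the point. Silence about site or baseline HAM-D is not proof that they will be left out. But the comparison of changes is stated outright, it differs from the endpoint definition, and nothing in the text says the baseline means will be constrained.

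Three stronger readings are tempting, and the article does not support them:

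- *No planned analysis accounts for either stratification factor.* The Medications section plans antidepressant covariates. They are not the stratum, but a flat denial would be wrong.
- *The plan gives up a full 10 points of power, partly through the strata.* Ten is the top of the range at ρ = 0.5 and needs a complete-case change test whose power is 80.7%, not the stated 84%. All of the computed gain comes from baseline HAM-D.
- *The change of rater biases the result.* Baseline precedes randomization by about a month, so the nurses cannot know the arm, and a systematic rater difference common to both arms cancels. The switch may lower the correlation, but no figure in the article shows this.

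**Conclusion.** The point holds as a correctable inconsistency with an efficiency cost. It is not a flaw that invalidates the trial. The endpoint is the 4-month HAM-D in two places and the analysis is of change in another; read as written, the change analysis does no better than ignoring baseline at the protocol's own ρ = 0.5. Baseline adjustment is worth about 7 to 10 points of power there. This rests on d = 0.5, 1:1 allocation, a two-sided 5% test and separate baseline means in the planned model. If the full plan already constrains the baseline means, the power gain disappears and only the wording needs reconciling. If the true correlation is near 0.7, the gain is about 2 points with d on the raw-score SD.

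The rater switch does not bias the arm contrast; it means only the 4-month score is rated by the blinded assessor, which is a further reason to make that score the outcome. Adjusting for site and the antidepressant stratum follows from the randomization design, with no claimed size.

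**What to change.** Reconcile Primary Outcome Measures with the Abstract and Trial Objectives by stating one primary depression analysis: the blinded assessor's 4-month HAM-D, compared between arms in a linear model with baseline HAM-D, site and antidepressant use at randomization as covariates. A repeated-measures model with a common baseline mean and the same two strata would serve equally well; if GEE is kept, say explicitly that the baseline means are constrained. Distinguish the antidepressant stratum, fixed at randomization, from later initiation or changes. Treat adherence in the same way, with the pre-randomization Wisepill month as the baseline covariate. In Sample Size Considerations, state the effect size and HAM-D SD behind the power figures.

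Baseline HAM-D, site, antidepressant status and the Wisepill month are all already collected, so the cost is analysis wording only.
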